**Methods:**

Design: prospective observational cohort study

Setting: regional UK ambulance and acute stroke services

Participants: a convenience series of two populations will be tested: adults with a label of suspected stroke assigned (and tested) by attending ambulance personnel and adults with a label of suspected stroke assigned at hospital (who have not been tested by ambulance staff).

Index test: SMARTChip Purine assay

Reference standard tests: expert clinician opinion informed by brain imaging and/or other investigations will assign the following diagnoses which constitute the suspected stroke population: ischaemic stroke, haemorrhagic stroke, TIA and stroke mimic conditions.

Sample size: ambulance population (powered for mimic sensitivity) 935 participants; hospital population (powered for mimic specificity) 377 participants.

Analyses: area under the receiver operating curve (ROC) and optimal sensitivity, specificity, and negative and positive predictive values for identification of mimic conditions. Optimal threshold for the ambulance population will maximise sensitivity, minimum 80%, and aim to keep specificity above 70%. Optimal threshold for the hospital population will maximise specificity, minimum 80%, and aim to keep sensitivity above 70%.

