### Sample size

Pilot study. There is no pre-specified sample size for the hospital pilot study. This phase will continue until agreement is reached about technical performance parameters as described below.Hospital cohort study. In the hospital setting, we consider that test specificity for mimics is more important than sensitivity such that mimics are directed away from the emergency stroke pathway whilst minimising removal of stroke patients in error. To detect a 90% (lower 95% confidence limit, 80%) diagnostic specificity for mimic identification assuming a mimic rate of 25% (i.e. 75% non-mimic or true stroke patients), one-tailed 5% type I error rate and 90% power, 167 participants (125 non-mimics) are required for the ‘per-protocol’ analysis. For validation of the hospital statistical model (combined clinical data and SMARTChip assay reading), 100 further non-mimics are needed, i.e. a further 134 patients in total. This gives a sample size of 301 (225 non-mimics). However, this target anticipates a non-mimic rate of 75% in the test population. If the mimic rate is higher, additional patients will be required. Inflating for 20% for participants who cannot feature in the ‘per-protocol’ analysis (see definition below in ‘Main hospital and ambulance study analyses’) gives an initial target sample size of 377 participants (including 281 non-mimics).Ambulance cohort study. In the pre-hospital setting, we consider that test sensitivity for mimics is more important than specificity to maximise removal of mimics from the emergency stroke pathway for service efficiency. To detect an 88% (lower 95% confidence limit, 80%) diagnostic sensitivity for mimic identification assuming a mimic rate of 40%, one-tailed 5% type I error rate and 90% power, 498 study participants (199 mimics) are required for the ‘per-protocol’ analysis (Agresti-Coull method [25]). For validation of the statistical model (combined pre-clinical data and SMARTChip assay reading), 100 further mimics are needed [26], i.e. a further 250 patients in total. This gives a sample size of 748 (299 mimics). However, this target reflects a typical FAST mimic rate of 40% amongst suspected stroke admissions. If the mimic rate is lower, additional patients will be required. Inflating for 20% of participants who cannot feature in the ‘per-protocol’ analysis (see definition below in ‘Main hospital and ambulance study analyses’) gives an initial target sample size of 935 patients (including 374 mimics).

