#### Statistical analyses

Objective 1: to determine the diagnostic accuracy of SMARTChip assay WBPC readings for identification of stroke mimic conditions when a reading is obtained in the pre-hospital setting, i.e. the test is conducted on patients suspected to have stroke by ambulance staff

For the PP group, logistic regression analyses with binary diagnosis of mimic or stroke (with TIA grouped with stroke as the intended purpose of the test is to identify mimic) as the outcome variable and WBPC reading as the explanatory variable will be used to construct a receiver operating curve (ROC) for all possible test thresholds. Area under the ROC curve and optimal sensitivity, specificity, and negative and positive predictive values, will be reported with 95% confidence intervals (CI). Optimal thresholds for sensitivity and specificity will be chosen. As we consider that test sensitivity is more important than specificity in the ambulance, the optimal threshold will be chosen to maximise sensitivity for mimics, minimum 80%, but aiming to keep estimated specificity for mimics above 70%. At lower levels of sensitivity and specificity, the test is unlikely to be considered of value.

For the ITT group, sensitivity and specificity will be calculated using a two-by-two table. Patients with a verified WBPC reading will be assigned a ‘test diagnosis’ according to the optimal threshold established in the PP analysis, and patients with an unverified WBPC will be assigned a test diagnosis of stroke. If the SMARTChip was deployed in clinical practice and an unverified reading was obtained, patients would continue to be managed as suspected stroke as there would be no extra information to exclude this possibility.
2.Objective 2: to determine the diagnostic accuracy of SMARTChip assay WBPC readings for identification of stroke mimic conditions when a reading is obtained in hospital, i.e. the test is conducted on patients suspected to have stroke by hospital staff and when an ambulance test has not been undertaken

For this objective, analyses as described above for objective 1 will be conducted. In terms of optimal thresholds, as we consider that test specificity is more important than sensitivity in hospital, the optimal threshold will be chosen to maximise specificity for mimics, minimum 80%, but aiming to keep estimated sensitivity for mimics above 70%. At lower levels of specificity and sensitivity, the test is unlikely to be considered of value.

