3.Objective 3: to develop pre-hospital and hospital statistical models which combine routinely available clinical data with SMARTChip assay WBPC readings to predict a stroke mimic diagnosis

Key variables will be added to the PP models described above to determine if this could significantly increase their accuracy. Clinical variables that would be available to ambulance/hospital staff will be included to reflect those available at the point of testing. Stepwise regression with backward elimination will be used to select the clinical covariates that most influence the diagnosis of mimics in conjunction with the WBPC readings.

A stepwise variable selection procedure will be used, and only variables that significantly improve the AIC will be retained in the model. Sensitivity, specificity, ROC AUC (with confidence intervals) and threshold will be reported if a suitable model is found.
4.Objective 4: to prospectively determine the diagnostic accuracy of the statistical models from objective 3

The models derived under objective 3 will be used to predict mimic/stroke status, and sensitivity, specificity and negative and positive predictive values will be reported with 95% confidence intervals (CI) for the PP population.
5.Objective 5: to report the failure rate of the SMARTChip assay when used in the pre-hospital and hospital settings

Reasons why a SMARTChip assay measurement was attempted but not obtained will be categorised and reported. This will include the following:
Failed SMARTChip calibration or bufferFailed SMARTChip reading following successful calibration (i.e. unverified reading)User-reported clinical or operational reason for aborting the calibration or reading process

A failure rate will be calculated for pre-hospital and hospital settings.
6.Subgroup and exploratory analyses

Diagnosis accuracy calculations will be performed on a pre-specified subgroup of the PP population consisting of only those patients with a reference standard diagnosis of ‘Definite Stroke’ and ‘Definite Mimic’ (this subgroup analysis is being undertaken as it considers the highest level of clinical confidence in the diagnosis and therefore allows exploration of the SMARTChip assay performance under ideal conditions). Contingent on the results of the study, it may be important to carry out some data-driven exploratory analyses. These will be determined post hoc and reported as such.
7.Substudy analysis

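### The ambulance cut-off rule puts its only minimum on sensitivity, which any test can reach, and leaves specificity above 70% as an aim, with no outcome stated if both cannot be met

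*Protocol article*

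**What the plan says.** In the Protocol article, Statistical analyses, objective 1, logistic regression of mimic versus stroke/TIA on the purine reading in the per-protocol group "will be used to construct a receiver operating curve (ROC) for all possible test thresholds". From that curve, "the optimal threshold will be chosen to maximise sensitivity for mimics, minimum 80%, but aiming to keep estimated specificity for mimics above 70" per cent. The abstract repeats the rule: "Optimal threshold for the ambulance population will maximise sensitivity, minimum 80%, and aim to keep specificity above 70" per cent. Objective 1 then adds: "At lower levels of sensitivity and specificity, the test is unlikely to be considered of value".

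The Sample size section explains the ambulance priority: "we consider that test sensitivity for mimics is more important than specificity to maximise removal of mimics from the emergency stroke pathway for service efficiency". It plans 498 per-protocol participants (199 mimics) to show 88% sensitivity with a lower limit of 80%.

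The hospital rule (objective 2) has the same form with the roles exchanged: "the optimal threshold will be chosen to maximise specificity for mimics, minimum 80%, but aiming to keep estimated sensitivity for mimics above 70" per cent.

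**The concern.** A minimum is useful in a decision rule only if some tests can fail it. Here the cut-off is free and sensitivity can always be raised by moving it, so a minimum on sensitivity excludes nothing. Specificity is the price paid for that move, and it carries no minimum. Taken literally, maximising sensitivity without a binding constraint runs to 100% sensitivity and 0% specificity. Only the aim prevents this, and the text does not say how far the aim may be missed.

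The gap matters when no cut-off meets both figures. The wording suggests that the minimum is kept and the aim is given up, but it does not say so, and it does not say that the test has then failed. The Discussion makes later deployment depend on satisfactory performance, and these sentences are where the article gives that word its numbers. The study could therefore report a cut-off that satisfies its stated minimum although specificity is well below the protocol's own 70%.

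**Working it through.** **Inputs.** Sensitivity minimum 80% and specificity aim 70% (objective 1). 498 participants with 199 mimics, 88% against 80%, one-tailed 5%, 90% power, 40% mimic rate (Sample size). Planned per-protocol non-mimics: 498 − 199 = 299.

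**1. The plan's own figure.** An exact one-sided binomial test of 80% against 88% with 199 mimics needs 169 detected (84.9%). Its type I error is 0.046 and its power 0.922. The one-sided Agresti-Coull limit gives the same cut: its lower limit is 79.7% at 168 of 199 and 80.3% at 169 of 199. Power stays at or above 90% from n = 198 with the exact test, against 199 stated. Then 199/0.40 = 497.5, rounded up to 498. The sample size reproduces and is not at issue.

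**2. An uninformative test.** With AUC 0.5, specificity = 1 − sensitivity, so 80% sensitivity gives 20% specificity. In 4000 simulated studies of such a test (199 mimics, 299 non-mimics):
- the 80% sensitivity minimum was met in all 4000;
- specificity at that point had a median of 20% (95% range 13% to 28%);
- 80% sensitivity and 70% specificity were met together in 0 of 4000.

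The minimum alone does not discriminate. The pair does.

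**3. Moderately informative tests.** Assume an equal-variance binormal ROC curve. Then d = √2 × z(AUC), specificity at 80% sensitivity = Φ(d − z(0.80)), and sensitivity at 70% specificity = Φ(d − z(0.70)), with z(0.80) = 0.842 and z(0.70) = 0.524.

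| AUC | d | Specificity at 80% sensitivity | Sensitivity at 70% specificity |
|---|---|---|---|
| 0.70 | 0.742 | Φ(−0.100) = 46% | Φ(0.217) = 59% |
| 0.75 | 0.954 | Φ(0.112) = 54% | Φ(0.429) = 67% |
| 0.80 | 1.190 | Φ(0.349) = 64% | Φ(0.666) = 75% |

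All three meet the stated minimum and miss the aim. None meets the pair.

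**4. AUC needed for both.** d = 0.842 + 0.524 = 1.366, so AUC = Φ(1.366/√2) = Φ(0.966) = 0.83.

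**5. Precision of a 70% floor.** An observed 209 of 299 (69.9%) has a 95% confidence interval of about 64% to 75% (Wilson or exact). A floor on the point estimate therefore does not exclude a true specificity somewhat below 70%.

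**The case against.** The strongest reply is that the protocol already treats both figures as its standard. The sentence after the rule names both measures, so a specificity of 20% or 46% is a result that the protocol itself says is unlikely to be of value. Where some cut-off does meet both figures, the natural reading of the rule picks the same cut-off as a constrained rule would. The AUC, specificity and predictive values are all to be reported with confidence intervals, so low specificity would be visible. The priority on sensitivity is deliberate and explained.

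Much of this stands. The two rules differ only when no cut-off meets both figures, and the priority itself is not at fault. What remains is that the sentence says unlikely, does not constrain the cut-off and does not define failure. The case it leaves open is the one in which a rule is needed.

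A reader might go further and infer that the study could endorse an unsafe triage threshold. The documents do not support that. They set no safety limit, the study is blinded and changes no treatment, and its deployment statement is conditional on acceptable performance. The phrase "mimics are directed away from the emergency stroke pathway whilst minimising removal of stroke patients in error" is the reason given for the hospital rule, where the minimum is on specificity; it is not a standard set for the ambulance.

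A reader might also count the strokes, or the candidates for reperfusion treatment, labelled mimic at exactly 80% and 70%. Those counts follow from the level of 70% and would be the same under a binding rule, so they do not measure this defect. Nor is the lack of a main-study breakdown by stroke type or treatment a finding. The one pre-specified subgroup is "only those patients with a reference standard diagnosis of ‘Definite Stroke’ and ‘Definite Mimic", but such tables are commonly left to the analysis plan, which is not shown.

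**Conclusion.** The concern holds as a defect in the decision rule. The only stated minimum excludes no test, the discriminating condition is not binding, and no outcome is fixed for the case where both cannot be met. The uninformative-test result needs no assumption about the shape of the ROC curve. The size for realistic tests (specificity of about 46% to 64% at AUC 0.70 to 0.80, and an AUC of about 0.83 for both figures) rests on the equal-variance binormal assumption, and the documents give no expected AUC.

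The hospital rule has the same form: 80% specificity is always attainable, and sensitivity is the aim. Its consequence is different, because a missed aim there means that fewer mimics are removed from the pathway. That is a loss of efficiency, not more missed strokes.

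**What to change.** In the abstract and under objectives 1 and 2, restate each rule as a constrained choice with the protocol's own figures.

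- **Ambulance:** choose the highest sensitivity among cut-offs with estimated specificity of at least 70%. The criterion is met only if that sensitivity is at least 80%.
- **Hospital:** choose the highest specificity among cut-offs with estimated sensitivity of at least 70%. The criterion is met only if that specificity is at least 80%.
- **Both:** if no cut-off qualifies, report that the criterion was not met. Give the 95% confidence interval beside the constrained measure.

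This keeps the stated priority in each setting and needs no extra patients or data. The cost is that the criterion can now fail: under the binormal assumption, a test with an AUC of 0.70 to 0.80 would be reported as reaching 59% to 75% sensitivity at 70% specificity, and so as not meeting it. A floor on the point estimate also leaves the uncertainty shown in step 5, which is why the interval should stand next to it. If the investigators want a different floor, or one on the lower confidence limit, its level is for the clinical team to set before the cut-off is chosen.

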## Discussion

Early diagnostic uncertainty about the cause of suspected stroke symptoms results in displacement of non-stroke mimic patients from more appropriate services, inappropriate demands on specialist resources and delayed access to specialist care and time-critical reperfusion therapies for stroke patients. Blood biomarkers have not previously been shown to be useful in emergency stroke assessment due to delayed elevation and a need for complex assays [13–15]. In addition, markers of inflammatory response or vascular risk have not improved upon clinical assessment alone [13, 28]. However, there is now evidence to suggest that blood purine concentration which rises rapidly during hypoxic tissue injury may be able to assist with urgent differentiation of stroke from mimic conditions [16–19].

This study will determine the performance of a portable point of care fingerprick measurement of blood purine concentration for the identification mimic patients within the suspected stroke population. We will also consider whether blood purine readings show greater diagnostic accuracy when combined with other information available to clinicians such as symptom severity. A substudy will explore whether serial purine readings could be an early indicator of large vessel occlusion which could be an alternative use of the test.

If test performance to identify non-stroke mimic conditions is satisfactory, future deployment in ambulances and emergency departments could assist with urgent triage of patients with suspected stroke symptoms and enable more appropriate direction of patients to stroke or non-stroke services. Improved service access could consequently result in better outcomes through faster access to appropriate treatments.

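### Objectives 3 and 4 test whether clinical data add to the assay but not whether the assay adds to clinical data, so the combined models' accuracy cannot be credited to the assay

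*Protocol article*

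**What the plan says.** All references are to the protocol article.

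Under Statistical analyses, objectives 1 and 2 fit a logistic model with mimic or stroke as the outcome, where "WBPC reading as the explanatory variable will be used to construct a receiver operating curve (ROC) for all possible test thresholds". The ambulance threshold is to "maximise sensitivity for mimics, minimum 80%, but aiming to keep estimated specificity for mimics above 70" per cent, and the hospital threshold is to "maximise specificity for mimics, minimum 80%, but aiming to keep estimated sensitivity for mimics above 70" per cent. The text adds that a test performing below these levels is unlikely to be of value.

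Objective 3 builds on those models: "Key variables will be added to the PP models described above to determine if this could significantly increase their accuracy". The selection step is described as follows: "Stepwise regression with backward elimination will be used to select the clinical covariates that most influence the diagnosis of mimics in conjunction with the WBPC". The retention rule is that "only variables that significantly improve the AIC will be retained in the model". For objective 4, "The models derived under objective 3 will be used to predict mimic/stroke status", and accuracy is reported for those models only.

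The Discussion states the same direction: "We will also consider whether blood purine readings show greater diagnostic accuracy when combined with other information available to clinicians such as symptom severity". The large vessel occlusion substudy also adds clinical variables to a WBPC model. No section mentions a model without WBPC, or a test of WBPC given clinical variables.

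**The concern.** The use proposed in the Background and Discussion is triage by staff who already have the history, symptoms and observations. The practical question is what a 6 to 8 minute test adds to that information. The comparison written into objective 3 answers a different question: what the clinical information adds to the test.

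The data collection lists include variables that may separate mimics from strokes without a blood test. Ambulance staff record possible seizure, blackout, headache, history of epilepsy or migraine, blood pressure and individual symptoms. Hospital staff record migraine and seizure history, among others. If these variables carry most of the discrimination, the combined model will perform well whatever WBPC contributes.

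The Discussion faults earlier inflammatory and vascular-risk markers for giving no gain over clinical assessment. As written, the study does not put its own assay to that test. The validation phases take 134 + 250 = 384 of the 301 + 748 = 1,049 patients planned before inflation (37%), and their results could not be attributed to the assay.

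**Working it through.** The plan gives no figure for this comparison, so there is none to reproduce. The check has three parts.

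**1. What 80%/70% means as an AUC.** With equal-variance binormal scores, the separation needed is d = z(0.80) + z(0.70) = 0.842 + 0.524 = 1.366. The AUC is Φ(1.366/√2) = 0.833. These levels are stated for WBPC alone; they are used below for the combined model only as a benchmark.

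**2. When a redundant assay could reach that level alone.** Suppose WBPC has within-group correlation ρ with the clinical score and adds nothing to it. Its own separation is then ρ·d_clin, where d_clin = √2·z(clinical AUC). It needs ρ ≥ 1.366/d_clin.

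- Clinical AUC 0.75: d_clin = 0.954, ratio 1.43, so not possible.
- Clinical AUC 0.85: d_clin = 1.466, so ρ ≥ 0.93.
- Clinical AUC 0.90: d_clin = 1.812, so ρ ≥ 0.75.

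**3. Simulation at the planned sizes.** Inputs from Sample size: ambulance 498 development and 250 validation, 40% mimics; hospital 167 and 134, 25% mimics. Assumptions not in the document: eight clinical variables, four of them informative; clinical-only AUC of 0.75, 0.85 or 0.90; and an assay that is either pure noise or redundant (ρ = 0.97). Clinical variables were removed backwards by AIC with WBPC kept in, and a clinical-only model was built the same way. There were 150 runs per row. Thresholds were set in development data at 80% sensitivity (ambulance) or 80% specificity (hospital).

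| Cohort | Clinical AUC | Assay | Assay AUC alone | Reaches 80/70 alone | AIC fall on adding clinical data | Validation AUC, combined / clinical only | Combined model, sens / spec |
|---|---|---|---|---|---|---|---|
| Ambulance | 0.75 | noise | 0.50 | 0% | 96 | 0.741 / 0.742 | 0.79 / 0.55 |
| Ambulance | 0.85 | noise | 0.50 | 0% | 205 | 0.846 / 0.847 | 0.79 / 0.74 |
| Ambulance | 0.90 | noise | 0.50 | 0% | 281 | 0.897 / 0.898 | 0.79 / 0.84 |
| Ambulance | 0.75 | redundant | 0.75 | 0% | 4 | 0.740 / 0.743 | 0.78 / 0.55 |
| Ambulance | 0.85 | redundant | 0.84 | 75% | 7 | 0.846 / 0.847 | 0.79 / 0.74 |
| Ambulance | 0.90 | redundant | 0.89 | 100% | 10 | 0.894 / 0.895 | 0.78 / 0.83 |
| Hospital | 0.75 | noise | 0.51 | 0% | 24 | 0.714 / 0.718 | 0.52 / 0.78 |
| Hospital | 0.85 | noise | 0.50 | 0% | 53 | 0.830 / 0.833 | 0.72 / 0.78 |
| Hospital | 0.90 | noise | 0.50 | 0% | 75 | 0.886 / 0.889 | 0.82 / 0.78 |
| Hospital | 0.75 | redundant | 0.74 | 3% | 2 | 0.724 / 0.715 | 0.54 / 0.77 |
| Hospital | 0.85 | redundant | 0.84 | 56% | 3 | 0.829 / 0.831 | 0.70 / 0.79 |
| Hospital | 0.90 | redundant | 0.89 | 94% | 3 | 0.889 / 0.892 | 0.81 / 0.79 |

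The noise rows show that the combined model's accuracy follows the clinical data: at 0.85 and above it comes close to 80/70 with nothing from the assay. In the redundant rows the planned comparison shows clinical data adding little to WBPC (AIC falls of 2 to 10), which invites the conclusion that the assay does the work. The comparison missing from the plan shows the lack of gain: combined minus clinical-only AUC lies between −0.004 and +0.009 in all 12 rows.

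**The case against.** A reader might infer that a useless assay could look successful without the study detecting it. The document does not support that. Objectives 1 and 2 report WBPC alone, with confidence intervals and stated performance levels; the noise assay reached those levels in 0% of runs. Only objectives 3 and 4 would flatter it.

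A reader might also infer that the combined model has to meet 80%/70%. It does not: those levels are set for objectives 1 and 2, and objective 3 says only that results follow if a suitable model is found.

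The AIC sentence does not exempt WBPC, so one could read it as letting WBPC drop out, which would be an indirect test of its contribution. The sentence before it limits selection to clinical covariates, so the text is ambiguous at best. On the generous reading, AIC keeps a single noise term with probability P(χ²₁ > 2) ≈ 0.16, and no clinical-only accuracy would be reported. The point does not go away, but the document cannot be said to rule such a test out.

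The main aim is the assay's own accuracy. Patients enter only after staff have assessed them and still suspect stroke, so some clinical filtering is built in. This stands, and objectives 1 and 2 are unaffected. The filtering does not adjust for the recorded variables, however.

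The redundant case needs a strong clinical model and a high correlation, as part 2 of the working shows, and neither quantity is in the document. This stands as a limit on how likely the problem is.

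Finally, a condensed article may leave an extra comparator model to an analysis plan, and nothing here forbids one. But the article does more than stay silent: it states the direction of the comparison and which models are validated.

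**Conclusion.** The concern holds in a limited form. Objectives 3 and 4 estimate the gain from adding clinical variables to WBPC and validate only combined models. They cannot show what WBPC adds, so the combined models' accuracy should not be credited to the assay. The standalone results of objectives 1 and 2 remain valid.

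The case that matters is an assay that is informative alone but redundant given clinical data. It could look good in all four objectives if the clinical-only AUC is about 0.85 or more and the correlation is high (at least about 0.93 at 0.85, or 0.75 at 0.90). At a clinical AUC of 0.75 it would almost never reach the standalone levels. These figures rest on binormal scores and assumed clinical AUCs; the document gives no value that would place the trial within that range. The change should be made before the models are built, because without it a claim of added value would have no support.

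**What to change.** In phases 2 and 4, also build a model from the same candidate clinical variables without WBPC, using the same transformation and selection method. State that WBPC stays in the combined model whatever its AIC contribution, and report a likelihood-ratio test for its term. That test is supportive only, since the accompanying clinical terms are chosen on the same data.

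Freeze both models and their thresholds. In phases 3 and 5, apply both to the same patients and report the paired difference in AUC with a 95% CI as the main measure, with the differences in sensitivity and specificity as secondary. Base any statement about the assay's added value on that difference.

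The cost is a few more model fits on data already being collected, with no extra patients or staff. The limit is precision in hospital: 134 validation patients with 100 non-mimics leave about 34 mimics. For one AUC of 0.85, the Hanley-McNeil variance is [0.1275 + 33 × (0.7391 − 0.7225) + 99 × (0.7811 − 0.7225)] / (34 × 100) = 0.0019, a standard error of about 0.044. Pairing should narrow the interval for the difference, but the report should say that the hospital estimate is imprecise and that a wide interval including zero does not show absence of added value.

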### Study design

Two prospective blinded observational cohort studies will be conducted, one involving a convenience series of suspected stroke patients tested by hospital services and one involving a convenience series of suspected stroke patients tested by ambulance services. There will be 5 phases:
Phase 1: pilot cohort study in hospital to review key technical performance parameters of the SMARTChip assayPhase 2: main hospital cohort study part 1. Once agreement is reached that technical performance is satisfactory, data will be collected to determine the diagnostic accuracy of WBPC assay readings for identification of mimic conditions (objective 2) and to build the statistical model (objective 3).Phase 3: main hospital cohort study part 2. Data will be prospectively collected to confirm the diagnostic accuracy of (i.e. validate) the hospital statistical model (objective 4).Phase 4: ambulance cohort study part 1. Data will be collected to determine the diagnostic accuracy of WBPC assay readings for identification of mimic conditions (objective 1) and to build the statistical model (objective 3).Phase 5: ambulance cohort study part 2. Data will be prospectively collected to confirm the diagnostic accuracy of (i.e. validate) the ambulance statistical model (objective 4).

Phases 4 and 5 may overlap with phases 2 and 3 depending on logistical factors, e.g. time taken to commence ambulance service involvement or availability of sufficient testing equipment.

Data collection to report the failure rate of the SMARTChip assay will run across phases 2–5. Data collection for the substudy is relevant to phases 4 and 5 only.

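### Whether clinical variables improve on the assay is judged only on development data, because the validation phases score the combined model without the WBPC-alone rule beside it

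*Protocol article*

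**What the plan says.** The Study design section of the protocol article ties objectives to phases. Phases 2 (hospital) and 4 (ambulance) estimate the accuracy of WBPC alone (objectives 2 and 1) and build the models (objective 3). Phase 3 is there to "confirm the diagnostic accuracy of (i.e. validate) the hospital statistical model (objective 4"), and phase 5 does the same for the ambulance model. The Sample size section follows this split. For the hospital accuracy analysis, "167 participants (125 non-mimics) are required for the ‘per-protocol’ analysis", and 134 further patients are added for model validation. The ambulance figures are 498 and 250.

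Under Statistical analyses, objective 3 poses the added-value question: "Key variables will be added to the PP models described above to determine if this could significantly increase their accuracy". It answers it by stepwise selection on the AIC. Objective 4 then says: "The models derived under objective 3 will be used to predict mimic/stroke status". The measures listed are sensitivity, specificity and predictive values with 95% CIs. Nothing in the article applies the WBPC-alone threshold to phase 3 or phase 5 patients.

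**The concern.** Objective 3 compares a WBPC-only model with a larger one on the data that chose and fitted the larger one. In-sample AUC tends to rise when selected covariates are added, whether or not they carry information. Phases 3 and 5 supply the independent patients who could correct this, but only one of the two rules is scored in them.

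A reader of the results would have two comparisons available, and neither is fair. The in-sample comparison favours the combined model. The other sets the combined model's validation figures against the WBPC figures from phases 2 and 4. Those come from different patients, and the WBPC threshold was itself chosen and scored on the same data, so this comparison flatters the assay.

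At stake is whether a service should adopt the assay alone or the assay plus a clinical model. The article's Discussion raises this when it says the study will consider whether readings are more accurate in combination with other clinical information.

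**Working it through.** **1. The plan's own figures (Sample size section).**
- Hospital: 125/0.75 = 166.7, so 167; 100/0.75 = 133.3, so 134; 167 + 134 = 301; 301/0.8 = 376.25, so 377.
- Ambulance: 199/0.40 = 497.5, so 498; 100/0.40 = 250; 498 + 250 = 748; 748/0.8 = 935.
- Requiring an exact one-sided 95% lower limit of at least 80% with 90% power gives 124 non-mimics (stated 125) and 198 mimics (stated 199). Power at the stated numbers is 92.7% and 92.2%.

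The stated sizes reproduce, and they show that 167 and 498 were set for the WBPC-alone analysis without the validation patients.

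**2. Share of per-protocol patients in the validation phases.**
- Hospital: 134/301 = 44.5%.
- Ambulance: 250/748 = 33.4%.

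**3. Which patients answer which question, by the Study design section.**

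| Phases | WBPC alone scored? | Combined model scored? | Independent of fitting? |
|---|---|---|---|
| 2 and 4 | yes (objectives 2, 1) | yes (objective 3) | no |
| 3 and 5 | not planned | yes (objective 4) | yes |

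The only cells holding both rules are those where fitting took place.

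**4. How large the in-sample advantage could be.** The article fixes neither the number of candidates nor the assay's AUC, so the inputs here are assumptions: WBPC AUC 0.80, and covariates that are pure noise. There were 10 candidates in the hospital cohort (167 − 125 = 42 mimics, 125 non-mimics) and 15 in the ambulance cohort (199 mimics, 498 − 199 = 299 non-mimics), with 120 to 500 runs per setting.
- *Plain AIC backward elimination.* Hospital: mean apparent AUC gain +0.017 to +0.023, positive in 72% to 82% of runs; true change in new patients, where scored, −0.020 to −0.022. Ambulance: +0.008 to +0.009, positive in 94% to 96%; true change −0.008 to −0.009.
- *Retention at p < 0.05*, one reading of the article's requirement that the AIC improve significantly. Hospital: +0.009, positive in 43%, no covariate kept in 57%. Ambulance: +0.004, positive in 47%, none kept in 53%. With five candidates, the gain was positive in about 20% of runs in both settings.
- *Four informative candidates* (assumed shift 0.5 SD). The true gain was about +0.035 in hospital and +0.06 in the ambulance. The hospital apparent gain was +0.074, an overstatement of 0.074 − 0.035 = 0.039.

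The direction of the optimism is stable. Its size is not.

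**5. What a paired comparison in the validation phases could resolve.** For a paired difference in proportions near zero, the 95% half-width is about 1.96 × √(d/n), where d is the proportion of patients the two rules classify differently. The article gives no d, so 10% to 30% is assumed.
- 100 key cases (non-mimics in phase 3, mimics in phase 5): 1.96 × √(0.10/100) = 6.2 points; 1.96 × √(0.30/100) = 10.7 points.
- Mimics in phase 3 (134 − 100 = 34): 1.96 × √(0.10/34) = 10.6 points; 1.96 × √(0.30/34) = 18.4 points.

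**The case against.** **The per-protocol group is not limited by phase.** The Analysis populations section defines it by a verified reading, a reference diagnosis and eligibility, and objectives 1 and 2 are run on that group. The Abstract also presents the full 935 and 377 as powered for the WBPC targets. This stands. A reader might infer that 384 of 1,049 planned per-protocol readings (37%) add nothing to the WBPC-alone objectives. That follows from the Study design and Sample size sections but not from the population definition, and the readings in any case serve objectives 4 and 5. Pooling all phases would not repair the comparison, since the WBPC threshold would then be chosen and scored on the pooled data, with no held-out comparison of the two rules.

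**The combined model is validated prospectively.** True, and its own accuracy will be estimated without development optimism. That does not say whether it beats the simpler rule.

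**No listed objective is a formal comparison, and an analysis plan could add one.** No objective in the Study objectives list asks for it. But the article itself poses the added-value question and assigns it to objective 3, so this is a stated choice of method rather than missing detail.

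**The WBPC-alone analysis is already adequately sized.** Correct by step 1. Adding validation patients would improve precision but corrects no error.

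**The comparison would be imprecise.** Also correct by step 5. An unbiased estimate with an honest interval is still better than a biased one that is never corrected.

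**Conclusion.** The concern holds in a limited form. Added value over the assay is judged on development data, objective 4 names no WBPC-alone comparator and no AUC, and so no unbiased comparison of the two rules is planned. The WBPC-alone threshold is likewise chosen and scored on the same patients. The patients who could serve both purposes are 44.5% of the hospital and 33.4% of the ambulance per-protocol targets.

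Two further inferences are not supported.
- *That the larger model will nearly always look better while being worse.* This requires every candidate to be useless and plain AIC retention. Under a significance rule the apparent gain was positive in fewer than half of the runs, and with informative candidates the true gain was positive.
- *That phases 3 and 5 would go unanalysed if no suitable model emerged.* The article's condition concerns what objective 3 reports. If every covariate is dropped, the model reduces to WBPC alone, and objective 4 would then score it in new patients.

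The conclusion rests on reading the phase allocation in the Study design section as governing. The simulated sizes rest on assumed candidates, assay AUC and retention rules.

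**What to change.** In objective 4, apply two locked rules to the same phase 3 and phase 5 patients: the WBPC-alone threshold from phase 2 or 4, and the combined model. Report AUC, sensitivity and specificity for each, with the paired differences and 95% CIs. Base any statement that clinical data increase accuracy on this comparison only, and acknowledge its limited precision, especially for sensitivity in hospital with about 34 mimics.

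State explicitly which phases feed objectives 1 and 2. Optionally, also report the WBPC-alone AUC over all per-protocol patients. At an assumed AUC of 0.80 its Hanley-McNeil standard error would fall from 0.044 to 0.033 (hospital) and from 0.021 to 0.017 (ambulance).

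The cost is a few sentences and a little more analysis, with no new patients or data. The reported benefit of the combined model may look smaller.
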